**Table Tabc:** 

Procedures in efficacy (active pediatric cohort)	Census and clustering Months −10 to −4	Enrollment/baseline(E) Visit 1, day 1	Study visit 2(E) Day 31 +/−3 days	Study visit 3(E) Day 61 +/− 3 days	Study visit 4(E) Day 91 +/−3 days	Study visit 5(E) Day 121 +/−3 days	Study visit 6(E) Day 151 +/−3 days	Study visit 7(E) Day 181 +/−3 days
Informed consent for census	X							
Demographic data collection	X							
Randomization	X							
Informed consent		X						
Anthropometry		X			X			X
Review infant vaccination card		X			X			X
Complete visit template		X	X	X	X	X	X	X
Malaria RDT		X	X	X	X	X	X	X
Malaria treatment ^a^		X	X	X	X	X	X	X
Assessment of selected NTDs		X	X	X	X	X	X	X
COVID response^b^		X	X	X	X	X	X	X
Malaria parasite immune response samples ^b^		X	X	X	X	X	X	X
*Plasmodium* PCR for quality control and molFOI^c^		X	X	X	X	X	X	X
Passive incidence surveillance at health facilities (all ages)		X-------------------------------------------------------X						

^a^Only if RDT is positive (see case definition)

^b^Only in a randomly selected sub-sample

^c^Only in a randomly selected 10% sub-sample

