#### Calculations

Based on the demographic data to be confirmed in the preceding census, the clusters are planned to include approximately 420 people, of which 280 will be above 4–5 years of age and potentially eligible for treatment and 140 will be children under 5 potentially eligible for follow-up. There will be 53 clusters per arm in Mozambique.

Clusters in Mozambique will be randomized in three arms, resulting in inclusion of approximately 45,000 participants to receive treatment or control and approximately 2000–4000 children to be followed for 6 months.

With this sample size, the study has 80% power at 5% significance to detect a 20% reduction in malaria incidence infection, from 4.20 cases/child-year at risk to 3.36 for the human-only intervention, using a coefficient of variation (km) of 0.35 for Mopeia/Mozambique. This value for km has been back-calculated from a cluster randomized trial recently conducted in the same study site [58].

For the human and livestock intervention, this sample size has 80% power to detect a further 20.5% reduction in malaria incidence infection between the human and human + livestock intervention arms, from 3.36 cases/child-year at risk (the lower incidence expected in the human only arm) to 2.67.

The total number of clusters needed per arm has been increased by one for all scenarios to account for potential LFU of a whole cluster (withdrawal of community consent, displacement, etc.)

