##### Efficacy analysis

The primary analysis will be the differential malaria incidence after the 6-month follow-up period between the intervention and control groups. Incidence will be based on monthly RDT results from the active cohort. Each RDT performed will be taken to represent one visit, which is equivalent to one child-month at risk. In the per-protocol correction, 14 days of time at risk for each treatment received (based on the post treatment prophylaxis provided by AL).

Differential incidence between intervention and control clusters will be assessed using a count data regression model accounting for the cluster design effect. Primary analysis will be assessed using generalized estimating equations.

Analysis in the multivariate model will be adjusted for potential confounders identified in the univariate analysis. Based on previous vector-control trials, the variables to be considered can be classified in the following categories: demographics (age and gender), socio-economics (head of household formal education, head of household occupied as a subsistence farmer, electricity in the household, livestock-human ratio, number of nets owned and distance to the nearest health facility), clinical (having experienced fever in the previous 48h, having slept under a bed net the previous night and infection of a sibling in the same household). A step-wise approach will be applied for building the final multivariate model, considering those variables with p-values lower than 0.20 in the univariate analysis.

To assess the bias due to LTFU, sensitivity analyses limited to participants who receive all treatments may be performed. Additional support will be obtained from a comparison of the baseline characteristics of individuals who remain vs. those that are LTFU.

Assessment of the direct benefit to the population that receives treatment will be done through passive surveillance at health facilities and cross-sectional studies to allow for a better risk-benefit analysis in this population.

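### The final efficacy model picks covariates by p-value, the protocol does not say whether the primary estimate comes from it, and the Day 1 RDT is not a candidate

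*Protocol article*

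**What the plan says.** Under Efficacy analysis, the protocol article first fixes the method: "Primary analysis will be assessed using generalized estimating equations". A separate paragraph then turns to adjustment: "Analysis in the multivariate model will be adjusted for potential confounders identified in the univariate analysis". It lists 11 candidates:

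- two demographic: age and gender;
- six socio-economic: the household head's education and farming occupation, then "electricity in the household, livestock-human ratio, number of nets owned and distance to the nearest health facility";
- three clinical, the last of them about siblings who share a home: "clinical (having experienced fever in the previous 48h, having slept under a bed net the previous night and infection of a sibling in the same".

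The paragraph closes with the selection rule: "A step-wise approach will be applied for building the final multivariate model, considering those variables with p-values lower than 0.20 in the univariate analysis".

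In the participant timeline for the paediatric efficacy cohort, the column "Enrollment/baseline(E) Visit 1, day 1" is marked for a malaria RDT, as are all six later visits. No footnote restricts the test to a subsample. The Calculations section sizes the trial "using a coefficient of variation (km) of 0.35 for Mopeia/Mozambique".

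**The concern.** There are three linked problems.

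- **Selection by p-value.** Screening on univariate p-values and then selecting stepwise lets the outcome data decide which covariates enter. A different sample could give a different model. The reported standard error treats the chosen set as if it had been fixed beforehand. Association with outcome also does not show imbalance between arms, so the screen does not identify confounders.
- **Which estimate is primary.** The text supports an unadjusted primary GEE with an adjusted supporting model, and equally a primary GEE that is the stepwise model. Two results could each be called primary.
- **The candidate list.** Malaria status at Day 1 is measured on the same scale as the outcome and, on the schedule, before the first round can have acted, yet it is not listed. Sibling infection, net use the night before and recent fever are listed with no statement that only the baseline value counts. If taken at follow-up visits, they could themselves be changed by the intervention, and adjusting for them would remove part of the effect. Sibling infection is the clearest case, and it is also the kind of variable that an outcome-based screen tends to keep.

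**Working it through.** **Inputs (Sample size and Calculations sections).** Control rate 4.20 and intervention rate 3.36 per child-year; between-cluster coefficient of variation 0.35; 14 children completing per cluster (sample size table, row for 20 eligible); follow-up 0.5 year, so 14 × 0.5 = 7 child-years per cluster; 80% power; 5% significance, taken as two-sided because the text does not say.

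**1. The plan's own figure.** Hayes–Bennett, unmatched rates: c = 1 + (1.96 + 0.842)² × V / (4.20 − 3.36)².

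- Within-cluster term: (4.20 + 3.36)/7 = 1.08.
- Between-cluster term: 0.35² × (4.20² + 3.36²) = 0.1225 × 28.93 = 3.54.
- V = 1.08 + 3.54 = 4.62, of which 3.54/4.62 = 77% is between clusters.
- c = 1 + 7.849 × 4.62/0.7056 = 52.43, rounded up to 53 per arm, as stated.

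Power at 53 per arm = Φ(0.84 × √(52/4.62) − 1.96) = 80.4%. No covariate enters this calculation.

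**2. What a Day 1 covariate could add.** Let r be the correlation between cluster Day 1 prevalence and the true cluster rate. The between-cluster term becomes 3.54 × (1 − r²). The documents give no value for r, so all of these are assumed:

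| r | V | Power at 53 per arm |
|---|---|---|
| 0 | 4.62 | 80.4% |
| 0.3 | 4.30 | 83.1% |
| 0.5 | 3.74 | 88.0% |
| 0.6 | 3.35 | 91.2% |

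**3. What the selection step does.** Simulation, 4,000 replicates: cluster-level log rates, two arms of 53 clusters, 14 children per cluster, 11 weak candidates (each correlated 0.15 with the cluster effect), p<0.20 screen, then backward removal at 0.05. The protocol does not give the candidate strength or the removal rule; both are assumed. With no true effect:

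| Model | Type I error | Model SE | Empirical SE |
|---|---|---|---|
| Unadjusted | 5.1% | 0.076 | 0.076 |
| Stepwise | 6.4% | 0.071 | 0.075 |
| All 11 pre-specified | 4.8% | 0.074 | 0.074 |
| Baseline RDT only | 4.7% | 0.067 | 0.067 |

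The stepwise standard error is about 5% too small (0.0714/0.0754 = 0.947). The last row assumes that the baseline RDT explains 30% of between-cluster variance.

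**4. A covariate affected by treatment.** In the same simulation with a true rate ratio of 0.80, the sibling variable was made to follow current transmission (loading 0.6, assumed). The stepwise estimate moved to about 0.86 and power fell from 81% to 58%. Fixing all 11 covariates in advance did not help (0.86 and 59%). The protection comes from restricting covariates to baseline values, not from pre-specification alone.

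**5. Is the Day 1 RDT an outcome or a baseline value?** The Efficacy analysis section counts each RDT as one child-month at risk and does not exclude Day 1. The schedule has seven RDTs (Days 1 to 181) over six months of follow-up. Read literally, a child would contribute seven child-months, the first of them from before any effect was possible.

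**The case against.** **The primary analysis may be unadjusted.** This stands as a reading. The GEE sentence and the multivariate paragraph are separate, and nothing says that the headline estimate comes from the selected model. A reader might infer that the primary confidence interval is invalid; the documents do not support that. They support an unresolved ambiguity, and a defect in any estimate taken from the selected model.

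**Adjustment has a rationale here.** This also stands. Clusters are randomised in Months −10 to −4, children consent at Day 1, and the Implementation section says that unblinded field workers recruit. The child cohorts could differ between arms for reasons other than chance, so it would be too strong to say that confounder adjustment has no place because the trial is randomised. The criticism is confined to choosing covariates by p-value.

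**Leaving out a precision covariate is not an error.** Correct. A reader might infer that the trial is underpowered without the Day 1 RDT. It is not: 53 clusters per arm gives 80.4% with no covariates. Nor do the documents show that the Day 1 RDT is the strongest predictor available; they rank none. Cluster prevalence would rest on about 17 enrolled children, and the protocol itself notes that HRP2 positivity can persist in up to half of treated cases at six weeks. Both would lower r. Some listed candidates, such as distance to a health facility, may already explain part of the between-cluster variation.

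**Covariate lists belong in the SAP.** Often so, but here the protocol states the rule itself, so the point concerns what is written and not what is missing.

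**Conclusion.** The point holds in a limited form. The protocol fixes a data-driven rule for its final multivariate model and does not say whether the primary estimate comes from it. Where that model is used, the expected harm from selection alone is modest: type I error of about 6.4% instead of 5%, under assumed candidate strengths and an assumed removal rule, in a cluster-level approximation to the GEE. The harm could be larger if a follow-up measure of sibling infection entered, but that depends on a timing the text does not give and on an assumed correlation. The gain from using the Day 1 RDT is extra precision of unknown size, from none at r = 0 to about 91% power at r = 0.6. The stated 80% power is not in question. The change is worth making because it settles all of these matters at almost no cost.

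**What to change.** Replace the screening and stepwise rule with one pre-specified primary model:

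- a GEE count model clustered on the randomised cluster, with arm, the child's Day 1 RDT result, cluster Day 1 RDT prevalence, age and sex;
- any further covariate named in advance and measured at baseline only, which applies in particular to fever, net use and sibling infection;
- a statement that this model gives the primary estimate, with the unadjusted model reported beside it;
- a statement that the Day 1 RDT is a covariate and is not counted as an outcome or as time at risk.

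The cost is a change of wording in the protocol and SAP, with no new data, and a few degrees of freedom among 159 clusters. The protocol article says that data collection was ongoing and the analysis team blinded at submission, and it provides for SAP updates with a record of when the plan was finalized. The change should be dated and made before unblinding.

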### Objectives {7}

Primary objective:

To determine the safety (in humans) and efficacy of ivermectin MDA (to humans or human and livestock simultaneously) for the prevention of malaria.

Note these co-primary objectives are determined in different populations. The efficacy endpoint is primarily measured in children under 5 years of age and safety is determined by anyone who receives the drug. Given the inclusion criteria, there might be a small overlap between the two populations.

Secondary objectives:To assess the efficacy of the intervention using complementary methods (efficacy)To assess the safety of the intervention with complementary methods (safety)To assess the PK of the proposed ivermectin dose/regime in its relationship with efficacy and safety outcomes (efficacy and safety)To assess the impact of ivermectin MDA at the proposed regimen on the prevalence of selected ectoparasitic NTDs (efficacy on NTDs and acceptability)To assess the relationship between malaria incidence in children and community prevalence at the peak of the malaria season (this serves for prevalence outcomes and paves the way for future studies or future evaluation using this outcome which could require fewer resources).To assess the relationship between active and passive surveillance for malaria at health facility (this serves as validation of passive surveillance and paves the way for future studies using this outcome which is much less resource-consuming while ensuring no key safety events are missed)To assess the accuracy for malaria diagnosis of two different malaria rapid diagnostic tests (RDTs) used in comparison to PCR (this is directly linked to efficacy as determined by RDTs)

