### Eligibility criteria {10}

Inclusion criteria:

For human treatment/safety cohortResidents of the study areaMale or female weighing more than 15kgAdult able to provide written consentMinors aged 12 to 17 able to provide assentParent/guardian’s ability to provide consent for minorsNegative pregnancy test for women aged between 13 and 49Agreement to adhere to study visits and procedures

For pediatric active cohort:Children in the age of highest burden at the time of enrollment (under 5 years of age)Residents of the study areaParent/guardian’s ability to provide consent for minors

For cross sectionalsResidents of the area for at least 3 months prior to enrolmentParent/guardian’s consent for minorsAbility to provide assent for minors aged 12 to 17Written consent from adults

For livestock treatment:Owner/guardian able to provide consentAnimal expected to spend at least one week every study month inside the cluster border

Exclusion criteria:

For human treatment/safety cohort:Known hypersensitivity to ivermectin or albendazoleRisk of Loa as assessed by travel history to Angola, Cameroon, Chad, Central African Republic, Congo, DR Congo, Equatorial Guinea, Ethiopia, Gabon, Nigeria, or SudanPregnant womenLactating women in the first week postpartumChildren < 15 kgCurrently participating in another clinical trialUnwilling to provide informed consent or assentUnwilling to adhere to study visits and/or proceduresSeverely ill either self-reported or in the eyes of the investigator, e.g., defined as the need for clinical care, or active or progressive disease interfering with activities of daily living. If in doubt, these criteria can be confirmed after a call with either the site PI/MD/safety officer against a pre-defined list.Currently under treatment with inhibitors of CYP3A or P-gp or other drugs that can interfere with the study

For active pediatric cohort:Non-residentsCurrently enrolled in other clinical trials

For cross sectionalsNon-residents

For livestock treatmentReceived ivermectin less than 4 weeks agoIntention to milk or slaughter the animal for human consumption during the withdrawal periodCalves under 8 weeks and piglets under 6 weeks of age.

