### Sample size {14}

The sample size is based on the main outcome (malaria incidence in a cohort of children followed prospectively in the cluster’s core area for six months), an outcome chosen based on WHO’s PPC for endectocides. This sample size has been corrected for cluster effect following Hayes and Bennett formula for unmatched rates [56].

The magnitude (20% reduction) was selected based on WHO’s recommended PPC for endectocides [57]. Additionally, the results of the RIMDAMAL trial suggest that a 20% reduction in malaria incidence can be achieved using a dosing regimen with a similar cumulative dose [40], these results although not statistically significant do point towards an expected effect size.

The final sample size is dependent on the population distribution as identified in the demography protocol.

The number of children per cluster can vary in order to streamline the cluster generation once the demographic data is available. The power, significance level, and target effect size will remain unchanged. The final number of clusters depends on the cluster size (the number of children in the active pediatric cohort recruited in the core of all clusters).

The target number of children to be included in every cluster is defined by the expected enrollment rate and loss to follow-up rate. We have estimated these as 15% and 20% respectively. So, for a cluster size to be 24 i.e., 24 children in the cohort finishing the study, the cluster must include 35 eligible children in the beginning (35 eligible of which an estimated 5 [15%] do not consent, 30 consent, of which 6 [20%] are LFU)

The number of clusters required increases exponentially as the number of children per cluster (cluster size) decreases. This is particularly marked below 13 children per cluster. The number of children presented is the number of eligible children required at the beginning, not accounting for 15% non-consenting and up to 20% LFU.

Peak incidence age: < 5 years

Power: 80%

Significance level: 5%

Expected incidence in the control group (λ0): 4.20

Expected incidence in the intervention (λ1): 3.36

Incidence reduction: 20%

Optimal cluster size: 20 children (assuming 3 non-consenting and 3 LFU)

Follow-up time: 6 months starting post-community dosing

Coefficient of variation (km): 0.35

People treated per cluster: approximately 300

Optimal total clusters required: 159 clusters (53 per arm)

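### The optional analysis meant to assess loss-to-follow-up bias restricts to participants who receive all treatments, which selects on dosing in a cohort that is mostly not dosed and so cannot serve that purpose

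*Protocol article*

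**What the plan says.** The primary outcome is infection incidence over six months in the active paediatric cohort. Under Efficacy analysis, "Incidence will be based on monthly RDT results from the active cohort", and each test performed counts as one child-month at risk.

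The same section turns to attrition with two sentences. The first is "To assess the bias due to LTFU, sensitivity analyses limited to participants who receive all treatments may be performed". The second is "Additional support will be obtained from a comparison of the baseline characteristics of individuals who remain vs. those that are LTFU". The section on non-adherence and missing data {20c} adds that the frequency and patterns of missing data will be studied for the main variables, and that multiple imputation will be considered if appropriate.

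On who is in which population, Objectives {7} states: "The efficacy endpoint is primarily measured in children under 5 years of age and safety is determined by anyone who receives the drug". It continues: "Given the inclusion criteria, there might be a small overlap between the two populations". Eligibility criteria {10} admit residents under 5 to the efficacy cohort with no weight limit, but require more than 15 kg for study drug. Sample size {14} plans for substantial loss; in its worked example of 35 eligible children, "30 consent, of which 6 [20%] are LFU".

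**The concern.** The restriction names receipt of treatment as its criterion, yet it sits in an analysis whose participants are mainly followed rather than treated. The trial is cluster randomised because ivermectin is expected to protect indirectly, through a community effect, and the cohort of young children is there to measure that effect. Keeping only the children who were themselves dosed changes the population and says little about the children who left.

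At stake is the reading of the main result. The target is a 20% reduction, about 20% of enrolled children are expected to be lost, and the article reports floods, cyclones and a cholera outbreak during the trial. If those lost differ in infection risk between arms, the rate ratio moves, and a reader will look to this sensitivity analysis to learn by how much.

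**Working it through.** **1. Does the set fit the cohort?** Setting the sections side by side:
- Efficacy outcome: children under 5, with no weight criterion (Outcomes {12}, Eligibility criteria {10}).
- Study drug, ivermectin or albendazole: residents above 15 kg; lighter children are excluded (Eligibility criteria {10}).
- Planned cluster: about 280 people above 4–5 years potentially eligible for treatment, listed separately from 140 under-5s potentially eligible for follow-up (Calculations).
- Efficacy-cohort visit schedule: no row for giving study drug (Participant timeline {13}).
- The treatment schedule does foresee some treated under-5s above 15 kg, so the overlap is not empty.

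That most cohort children receive no study drug is therefore a sound inference, but no proportion is stated. If, purely as an assumption, between 5% and 30% of the 2162 children expected to complete were dosed, the restricted set would hold between 0.05 × 2162 = 108 and 0.30 × 2162 = 649 children across three arms.

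**2. Does the set track follow-up?** Study drug is given on Days 1, 31 and 61. Efficacy visits run to Day 181. A child dosed three times can still be lost at any time in the last 181 − 61 = 120 days, and a child too light to be dosed can attend every visit. The criterion measures adherence to dosing, not retention.

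**3. What else could the phrase mean?**
- Completers, or all visits attended: the primary analysis uses every test performed, so children later lost contribute their earlier visits. Comparing that estimate with one from completers shows whether partly observed children differ. It says nothing about infections after they left.
- Artemether-lumefantrine: the same section uses treatment in this sense when it describes the 14-day correction of time at risk. It is given in the cohort only after a positive test, so restricting on it conditions on the outcome.

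**4. The planned loss.** From the sample size table, 159 clusters × 20 eligible children = 3180; 3180 × 0.85 = 2703 enrolled; 2703 × 0.80 = 2162 completing. This reproduces the plan's figures. Expected loss is 2703 − 2162 = 541 children, or 20%.

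**5. What such loss could do (illustration).** The assumptions, none of them from the documents, are:
- the observed ratio is 0.80;
- lost intervention child-time has control-level incidence;
- loss in controls is non-informative.

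With m the share of intervention child-time lost, true ratio = (1 − m) × 0.80 + m × 1.00.
- Loss spread evenly over follow-up: m = 0.20 × 0.5 = 0.10, so 0.90 × 0.80 + 0.10 × 1.00 = 0.82, an 18% reduction.
- All lost children contributing nothing: m = 0.20, so 0.80 × 0.80 + 0.20 × 1.00 = 0.84, a 16% reduction.

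**The case against.** The best defence is that this is one optional sentence among several safeguards. The article also compares baseline characteristics of those who remain and those lost, undertakes to study missing-data patterns, and leaves room for multiple imputation. Additional analyses are referred to the SAP, which is not shown. Outcome assessors are blinded although the trial is open-label. Much of this stands: a reader might infer that the restricted analysis is the only check on attrition, and the article plainly contradicts that. What remains is that a baseline comparison can show that the lost differ, but cannot say by how much the rate ratio would change, and imputation is only to be considered. Nor is this a detail left to the SAP: the article states a method and its purpose, and the two do not match.

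Three further inferences go beyond the text:
- That nearly the whole cohort would be discarded: the article says the overlap might be small and gives no share.
- That a completers-only analysis would be empty: it is weak, but the comparison with all available visits carries some information.
- That 0.84 is the bias to expect: this equates 20% of children lost with 20% of child-time lost, and no section supports full reversion to control incidence among lost intervention children. Bias could also run the other way.

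**Conclusion.** The concern holds for this one sensitivity analysis. Read literally, the restriction keeps a selected minority of the efficacy cohort, chosen by weight and by adherence to Day 61, and cannot assess bias from loss up to Day 181. Neither alternative reading rescues it: completers give a weak check that leaves unobserved outcomes untouched, and malaria treatment conditions on infection. No stated check commits to quantifying the effect of loss on the rate ratio.

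The figures of 0.82 and 0.84 show the scale that such an analysis should be able to examine; they rest wholly on the stated assumptions and are not predictions. That the restriction drops most of the cohort rests on the weight criterion and the expected small overlap. A reader might infer that the primary analysis or the sample size is undermined. It is not: an optional sensitivity set feeds into neither. The point should be corrected, but it does not threaten the trial.

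**What to change.** Replace the sentence with a sensitivity analysis on the full active cohort, in two parts:
- The primary GEE model weighted by the inverse probability of attending each visit, with attendance modelled on arm, Day 1 RDT, age, household variables and the previous RDT result. Equivalent multiple imputation would also serve.
- A tipping-point analysis that raises assumed incidence in the missed child-months of the ivermectin arms until significance is lost, reporting how extreme that assumption has to be.

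Keep the baseline comparison of remainers and lost as supporting description. If an analysis by receipt of treatment is still wanted, define which treatment is meant and label it an adherence analysis. Repeating the primary analysis without cohort children who were themselves dosed is a separate, optional analysis of the indirect effect; it should not be presented as a check on attrition.

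The inputs are already collected, so the cost is a change of SAP wording, modest programming and somewhat wider intervals. The article provides for SAP review before close-out and reports that the analysis team was still blinded at submission, so the change should be documented before unblinding.
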